### Quality of life and mental health

#### Health related quality of life

Is assessed using the Short Form-36 (SF-36) [113, 114]. This instrument is validated and has been successfully used in samples of long-term CCS [115–119]. It consists of 36 questions that can be summarized into eight scales: physical functioning, role limitation due to physical health (role limitation physical), bodily pain, general health perception, energy & vitality, social functioning, role limitation due to emotional problems (role limitation emotional), and mental health. The eight scales can be further aggregated into a Physical Component Summary (PCS) and a Mental Component Summary (MCS) [114]. We will convert raw scores into T-scores (mean = 50, SD = 10, range 0–100) according to age- and sex-stratified norm data from a public use-file of the German Federal Survey (*N* = 6964) because no Swiss data of the SF-36 are available [113].

#### Fatigue and actual well-being

Is assessed with a Visual Analogue Scale (VAS) and the Checklist Individual Strength (CIS). A VAS for fatigue and well-being is designed to measure these characteristics, which are believed to range across a continuum of values and cannot easily be measured directly. Operationally, the VAS is a horizontal line, 100 mm in length, anchored by two word descriptors at each end. In our study, the descriptors will range from ‘not tired at all’ to ‘completely exhausted’ for fatigue and from ‘feeling absolutely miserable’ to ‘perfect well-being’ for well-being. The CIS is a validated 20-item questionnaire, that is designed to measure four aspects of fatigue that may have been experienced during the previous 2 weeks, i.e. severity of fatigue (8 items), concentration (5 items), motivation (4 items) and physical activity (3 items) [26, 120, 121]. Each item is scored on a 7-point Likert scale. The total score is the sum of the scores 1–7 in the 20 items (range 20–140). Norm scores are available for different patient groups and healthy people. The CIS has also been successfully used in long-term survivors of childhood cancer [26]. The CIS showed to have good internal consistency and validity across studies and could successfully discriminate between non-fatigued and fatigued groups and cut-off points for clinical levels of fatigue have been developed [26, 122, 123].

#### Mental health

Psychological distress will be assessed using the Brief Symptom Inventory (BSI) [124]. The BSI is a widely used and well-validated instrument to screen the following nine domains of distress: somatization, obsessive-compulsive tendencies, interpersonal sensitivity, depression, anxiety, aggression, phobic anxiety, paranoid ideation, and psychotic tendencies. Responses to all 53 items can be further summarized in the Global Severity Index (GSI). For each item, participants express how much they agree with a statement describing the previous 7 days on a 5-point Likert-scale ranging from 1 (not at all) to 5 (very much). Scores from all scales will be transformed to T-scores (mean = 50, SD = 10, range 0–100) according to the German norm population [125]. A T-score of ≥63 on any scale corresponds to the 90th percentile of the norm population and indicates a risk for being at significant psychological distress in this area (case rule) [125].

### Personal history and clinical examination

A thorough personal history, study of the medical record and clinical examination is performed in each participant, with special emphasis on the cancer history, signs and symptoms of cardio-metabolic, pulmonary or neurological diseases, health behaviour, medical doctor visits, hospitalizations, and medications [126–128]. Symptoms, medical doctor visits, hospitalizations and medications are updated after 6 and 12 months. Physical examination of the lungs, heart, abdomen, joints, extremities, ears, mouth, lymph nodes and a detailed neurological status are performed at baseline and after 6 and 12 months. Vital parameters including heart rate and blood pressure are taken at every visit. Tanner stadium is assessed once at baseline and only repeated after 6 and 12 months if the participant is not fully mature at baseline [129]. Socio-demographic characteristics are assessed by questionnaire at baseline, health behaviours at baseline and after 12 months, using standardized questions from the Swiss Health Survey and the Swiss Census [126–128].

### Adverse events and exercise related complications

Every adverse event including exercise related complications [130] whether or not causally related with the exercise training will be monitored based on standardized procedures and followed until resolved [131]. Each adverse event is recorded in the REDCap database and classified based on The Common Terminology Criteria for Adverse Events (CTCAE) [131]. Serious adverse events are reported to the sponsor and the responsible independent ethics committee. An independent safety auditor of the University Children’s Hospital Basel (UKBB) is monitoring patients’ safety throughout the study period.

Participants who show an elevated blood pressure or a pathological oral glucose tolerance test at baseline or during a study visits, can enter/stay in the study, but are referred to the family physician or a specialist to get the appropriate treatment. In case of diabetes, the participant will enter the study once a stable condition is reached but earliest after 3 months.

Participants at risk for cardiac late-effects due to cardio-toxic childhood cancer therapy (anthracyclines and/or chest radiation) can enter the study normally, but are recommended to get a cardiac assessment with an adult cardiologist according to recent recommendations [132].

#### Physical activity intervention (intervention group)

Survivors in the intervention group are asked to add at least 2.5 h of intense physical activities per week. These should include 30 min of strength building exercises and 2 h of aerobic exercises per week. Exercise bouts lasting 20 min or longer are counted towards the total weekly training time. This “dose” of physical activity is based on the international recommendations of healthy physical activities from the Centre of Disease Control and Prevention (CDC; www.cdc.gov) [133].

Based on the initial exercise test, general health status and participant’s preferences and motivation, subjects of the intervention group receive a counselling at the second visit of the baseline assessment (T0b; Fig. 1
**,** Additional file 2: Table S1). A standardized approach is used to assess survivors’ preferences with respect to physical activities, identify possible barriers and determine the individual motivation to start specific activities. Based on this assessment, individualized physical activities are defined and implemented into the participant’s daily life. Survivors of the intervention group are also motivated to incorporate activities of moderate intensities into daily life such as walking instead of driving or climbing stairs instead of taking the escalator. Participants are also advised to reduce inactive behaviour such as television viewing, computer games, etc. with the aim of reducing 25% of their actual media time. The motivational interview is performed by one of the project physiotherapists who have been trained prior to the study.

For motivational reasons each survivor of the intervention group is equipped with a step counter (pedometer, Model Fitbug Air) and asked to document daily steps. Participants keep a daily training log using a web-based platform with individual anonymous logins. Data on 1) strenuous exercise performed that day (type of exercise, duration), 2) step counts (overall and aerobic steps), 3) media-related sedentary time and sleeping hours, and 4) mood and well-being are entered and graphically displayed to give the participants an immediate feedback about their progress. The participants receive a “reminder” message on his or her mobile phone or via email if no entries are made for three consecutive days. If there are no entries for a whole week, the survivor is contacted by phone by his “personal coach” (physiotherapist). There are also scheduled phone contacts after 1, 2, 4, 5, 8 and 10 months of the intervention to discuss compliance, motivation, and progress and to re-counsel the survivors on their training plan. Training logs and physical activity behaviour are checked and discussed during the clinic visits (at months 3 and 6), and exercise counselling is repeated.

After the 1-year assessment, participants of the intervention group can keep their step counters and will still have access to the web-based training log to report and view their activity data, but no further support is given from the research team. A follow-up after 1–2 years off trial is planned but this is not subject of the current study protocol.

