### Secondary outcomes

Secondary outcomes are differences in change between the intervention and control group from baseline to 6 months for the composite cardiovascular disease risk score, and from baseline to 6 and 12 months for the single CVD risk factors, glycaemic control, bone health, body composition, physical fitness, physical activity, quality of life, mental health, fatigue and adverse events (safety). Additional file 2: Table S1 lists all assessed outcome variables.

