### Study design

This study is a single-centre RCT including childhood cancer survivors from various paediatric oncology clinics of Switzerland. Control and intervention arms run parallel (Fig. 1). Assessments are performed at baseline (T0) and after three (T3), six (T6), and 12 (T12) months. The assessments at T0, T6 and T12 comprise of two visits (a and b, respectively) in the study centre, 14 days apart, and T3 of one visit. Randomization is performed after the first visit of T0 (T0a) (Additional file 2: Table S1**,** Fig. 1). A motivational interview for the intervention group is performed at the second visit of T0 (T0b). After the intervention period, controls are offered a similar personalized exercise programme without long-term coaching (see paragraph on physical activity intervention). Eligible participants are contacted, informed and, if consenting, enrolled into the study (see paragraph on recruitment) until we reach the pre-defined number of participants.

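### Adverse events are compared between arms, but the intervention arm has at least twice as many scheduled contacts, so the comparison of minor events is open to detection bias

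*Protocol article*

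**What the plan says.** **Outcome.** Under Secondary outcomes, "Secondary outcomes are differences in change between the intervention and control group", and the list ends with "quality of life, mental health, fatigue and adverse events (safety". Publication policy places the safety endpoints in the main paper.

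**Recording.** In the section Adverse events and exercise related complications, the rule is: "Every adverse event including exercise related complications [130] whether or not causally related with the exercise training will be monitored". Events are recorded in REDCap under standardised procedures. The section does not say at which contacts they are elicited.

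**Contact in both arms.** Study design gives T3, T6 and T12 to everyone: "T6 and T12 comprise of two visits (a and b, respectively) in the study centre, 14 days apart, and T3 of one visit". It also says "Randomization is performed after the first visit of T0 (T0a", so the second baseline visit, T0b, falls after allocation. Under Personal history and clinical examination, which covers each participant, "Symptoms, medical doctor visits, hospitalizations and medications are updated after 6 and 12 months". T3 is not named there.

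**Contact in the intervention arm only.** Under Physical activity intervention: "There are also scheduled phone contacts after 1, 2, 4, 5, 8 and 10 months of the intervention". There is a daily web diary, which includes mood and well-being, and a reminder after three days without entries. After a longer silence, "If there are no entries for a whole week, the survivor is contacted by phone". The Compliance section describes the telephone contacts as monthly, which does not match six calls. Under Blinding, the project physiotherapists, who do the coaching, cannot be blinded.

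**The concern.** A between-arm comparison of adverse events is fair only if an event has about the same chance of being recorded in either arm. Here the contact schedule depends on the arm. A strain or short illness in month 7 can come up at the month 8 call in the intervention arm. In the control arm it waits for the T12 visit. A gap in the diary, which an injury or illness may cause, prompts a call in one arm only. Because every event is to be recorded, an injury mentioned on a coaching call belongs in the database.

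The comparison would then mix true harm with intensity of surveillance. It could suggest an excess of minor harm from exercise that does not exist, or blur one that does. The primary outcome is not touched. What is exposed is the safety comparison planned for the main paper.

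**Working it through.** **The plan's own figure.** The number per arm used below is the Sample size section's 75, from 60 with complete data and 20% loss: 60 / (1 − 0.20) = 75. It reproduces. The article gives no adverse-event rate.

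**Step 1. Scheduled contacts after allocation** (Study design; Physical activity intervention; Compliance). In every row, the intervention count is the control count plus the calls.

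| Counting rule | Control | Intervention, six calls | Ratio | Intervention, monthly read as 12 calls | Ratio |
|---|---|---|---|---|---|
| Time points T3, T6, T12 | 3 | 3 + 6 = 9 | 3.0 | 15 | 5.0 |
| Each centre visit (T3, T6a, T6b, T12a, T12b) | 5 | 5 + 6 = 11 | 2.2 | 17 | 3.4 |
| Centre visits plus T0b | 6 | 6 + 6 = 12 | 2.0 | 18 | 3.0 |

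The lowest ratio on any count is 2.0. Diary prompts and calls triggered by missing entries are not counted.

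**Step 2. Gaps between contacts.** Control contacts at months 3, 6 and 12 leave gaps of 3, 3 and 6 months. Intervention contacts at months 1, 2, 3, 4, 5, 6, 8, 10 and 12 leave six gaps of 1 month and three of 2 months. The longest gap is 6 v 2 months. For events spread evenly over the year, the mean wait to the next contact is Σg² / (2 × 12):
- control: (9 + 9 + 36) / 24 = 2.25 months
- intervention: (6 × 1 + 3 × 4) / 24 = 0.75 months

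**Step 3. Illustrative size.** Assumptions, none from the documents: equal true rates; an event can be reported only at the next contact; a call counts like a visit; the chance of reporting halves every h months. The share recorded is D = (1/12) × Σ (h / ln 2) × (1 − 2^(−g/h)), summed over the gaps g.

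For h = 3, h / ln 2 = 4.328:
- control: 4.328 × (2 × 0.5 + 0.75) / 12 = 0.631
- intervention: 4.328 × (6 × 0.2063 + 3 × 0.3700) / 12 = 0.847
- ratio: 0.847 / 0.631 = 1.34

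The chance of a falsely significant difference uses a two-sided 0.05 Wald test of the log rate ratio, with SE = √(1/(75λD_control) + 1/(75λD_intervention)) and λ = 1 event per person-year, also assumed.

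| Half-life h (months) | Recorded, control | Recorded, intervention | Ratio | Chance of false significance |
|---|---|---|---|---|
| 1 | 0.329 | 0.631 | 1.92 | 0.75 |
| 3 | 0.631 | 0.847 | 1.34 | 0.33 |
| 6 | 0.783 | 0.919 | 1.17 | 0.15 |
| 12 | 0.882 | 0.958 | 1.09 | 0.08 |
| 24 | 0.938 | 0.979 | 1.04 | 0.06 |

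With λ from 0.5 to 2, the last column runs from 0.46 to 0.96 at h = 1 and from 0.05 to 0.07 at h = 24.

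**Step 4. After the fix.** If only questioning at T3, T6 and T12 counts, the gaps are identical in both arms. In this model the ratio is then 1.00 and the false-positive rate 0.05.

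**The case against.** The strongest reply is that no section says adverse events are collected through the calls or the diary. The calls are described as covering compliance, motivation and progress, and the diary has no injury or symptom field. Standardised procedures, operating procedures and additional files exist that are not shown, and an article commonly leaves elicitation detail to them. Unequal contact is also inherent when coaching is the treatment.

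Much of this stands. Detection through calls is an inference, and a common elicitation schedule may exist elsewhere. But the rule that every event is recorded does not exempt one disclosed on a call, and uniform classification does not create equal opportunity when the schedules differ by arm.

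Three stronger readings are tempting and are not supported:

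- **Three times as many contacts.** With six calls, this holds only by time point. By visit the ratio is 2.0 to 2.2.
- **Controls updated only at 6 and 12 months.** That update applies to each participant, so it is a shared safeguard and already part of the remedy.
- **Surveillance will look like harm.** This depends on assumed capture rates. Take a true risk of 40% in both arms, with 90% v 60% of events captured. The observed counts are 75 × 0.40 × 0.90 = 27 and 75 × 0.40 × 0.60 = 18, a ratio of 1.5. The pooled proportion is 0.30, so z = 0.12 / √(0.30 × 0.70 × 2/75) = 1.60 and p is about 0.11, above the plan's 0.05. With 90% v 75% captured, the ratio is 1.2.

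The coach call is also triggered by missing diary entries, not by measured inactivity, so it is only an indirect marker of illness or injury.

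**Conclusion.** The point holds as a risk of detection bias, not as a demonstrated false signal. The documents themselves establish four facts: adverse events are compared between arms, every event is recorded, scheduled contact is at least twice as frequent in the intervention arm, and nothing shown equalises detection between visits.

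The size is conditional. Under equal true rates, recorded minor events could be about 1.2 to 1.9 times as frequent in the intervention arm if the recall half-life is 6 months down to 1 month. For serious or well-remembered events, such as hospitalisations, the ratio is close to 1 (1.09 and 1.04 at half-lives of 12 and 24 months). These figures rest on assumed event rates and recall, and on calls being a route by which events reach the database. If they are not such a route, and the diary and no-entry calls are not either, this source of bias largely disappears, but the article does not say so.

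The six calls under Physical activity intervention and the monthly contacts under Compliance contradict each other and must be reconciled.

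**What to change.** 1. Ask the same structured adverse-event question (symptoms, injuries, doctor visits, hospitalisations since the last visit) in both arms at the existing T3, T6 and T12 visits. This extends the current 6- and 12-month update to T3.
2. Tag each event in REDCap, when it is entered, by how it was found: common visit, call or diary, or spontaneous report. The source is hard to reconstruct later.
3. Make the main between-arm comparison of non-serious events the one based on common-visit elicitation.
4. Report the all-source comparison beside it, so that no known intervention-arm event is hidden. Leaving call- or diary-found events out altogether could understate harm.
5. Compare serious events whatever their source.
6. Reconcile the two statements of the call schedule.

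Recording and follow-up of events stay as they are. The cost is one extra database field and a few minutes at T3, and some intervention-arm events will count only in the all-source table. Identical questions reduce differences in recall but do not remove them: intervention participants keep a daily log and may already have discussed an event with their coach, or may not repeat at a visit what they have already reported.

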#### Control group

The control population of this study is asked to keep its activity level constant over the one-year study period. With this study, we will be able to test the effect of *additional* physical activity compared to a “normal” activity level. After the one-year study period, participants of the control population have the opportunity to receive the same personalized physical activity counselling and motivational interview, but without personal follow-up coaching. They also receive a step counter and access to the same web-diary, which they can use to follow their physical activity plan.

#### Compliance

Compliance of the participants is assessed by different means. This will allow us to validate whether the aims of the intervention and control arm have been maintained and to make dose-response analyses for physical activity in this population.

Participants of the intervention group daily report the pedometer steps and sports performed in the web-diary, they are contacted immediately in case of non-compliance, they have monthly telephone contacts with the physiotherapists, and three-to-six-monthly assessment visits with the physicians, physiotherapists and other staff. After the one-year intervention, a structured interview is performed with the participants of the intervention group to assess their opinion on the intervention, their compliance, reasons for compliance or non-compliance and readiness to continue the physical activity programme. Furthermore, at each study visit (3, 6, and 12 months), the retained steps of the pedometers over 2 weeks prior to the visits are (unknown to the participants) downloaded and entered into the study database to assess how accurate participants of the intervention group report their daily steps in the web-diary.

Participants of the intervention and control group report their actual activities at each visit (T3, T6, and T12) and we objectively measure the activity levels at T6 and T12.

#### Blinding

With our physical activity intervention, it will not be possible to blind the study participants themselves, the project physiotherapists, the project physicians and some of the assessors. But wherever possible all other members of the project team will be blinded for group allocation of the participants, i.e. those who perform the DXA measurement, the physical performance test, the blood analysis, the quality check of the data in the database and the statistical analysis.

#### Sample size

A study by Kriemler and colleagues using the same CVD risk score showed a reduction in the z-score by 14% after a 1-year physical activity intervention in children and adolescents [34]. Our population is older with a history of cancer, intensive treatments and long hospitalisations. We therefore expect higher CVD risk in this population at baseline and even greater changes after an intervention. To be conservative, this study is powered to detect a difference between the intervention and control group of 15% (no change in the control group and 15% change in the intervention group) after the 1-year intervention. For a power of 0.80 and a two-sided type 1 error probability of 0.05, 60 survivors with complete data are required in each study arm. Assuming that 20% of participants will dropout or have missing data, 75 survivors have to be recruited in each arm. From the Swiss Childhood Cancer Registry we identified 4241 eligible 5-year survivors of whom about 1500 were diagnosed and treated in one of the three Swiss Paediatric Oncology Group (SPOG) clinics of initial recruitment (Basel, Lucerne, and Zurich) [3]. Therefore, with an expected participation rate of 20% of the survivors contacted and invited, we will reach a sufficient sample size.

#### Data analysis

Descriptive statistics will be used for clinical, sociodemographic and prognostic variables measured at baseline (stratified by intervention and control group). We will use frequencies and proportions with 95% confidence intervals (CI) for categorical variables and mean with ±SD or 95% CI (or median and range) for continuous variables. Descriptive analysis of baseline characteristics will be performed as soon as the baseline assessments are completed for all participants. This cross-sectional analysis will inform about the comparability of the treatment groups and the need for adjustment of between treatment group comparisons. Furthermore, baseline assessments will provide important results about characteristics, health behaviours and health status of long-term CCS in Switzerland. We will also compare the distribution of baseline sociodemographic characteristics to the Swiss Childhood Cancer Registry, to estimate the representativeness of our sample.

The primary analysis will be conducted as intention-to-treat analysis (ITT) for the primary outcome (change in composite CVD score from T0 to T12). All participants will be analysed in the group where they were originally allocated and missing data will be imputed by means of last observation carried forward (LOCF) [134]. LOCF is an appropriate procedure in this setting because it will lead to more conservative effect estimates (i.e. towards the null), because lost to follow-up is more likely to occur in the intervention group (because of an intensive and time-consuming programme) which is the group expected to change (improve). Attempt will be done to follow up all randomised participants, even if they withdraw from the allocated treatment. If the parameters of the composite CVD risk score are skewed, they will be transformed to reach normal distribution for calculating the z-scores.

The secondary analyses include several steps: *First*, we will do the same ITT analysis with appropriate means of imputation of missing data for all the secondary outcomes. *Second*, we will perform sensitivity analysis on the primary and all secondary outcomes, including, a) complete data (complete case analysis), i.e. observations with missing information on relevant variables will be dismissed; b) analysis of intermediate effects after 3 and 6 months of intervention; c) dose-response analysis based on the actual physical activities (min of vigorous physical activities per week) or physical performance (VO_2_peak) during the period of interest, independent of the group allocation; and, d) per protocol analysis.

Per protocol analysis will include several analyses based on the actual “treatment” that the participants adhered to (independent of group allocation), first based on the reported compliance and second based on the assumed compliance. In the first analysis based on the *reported compliance*, the following participants will be analysed as being in the “intervention group”: participants randomized into the intervention group who reported in the web-diary to have reached at least 2/3 of the target physical activity (addition of 100 min of moderate to vigorous physical activities [MVPA]); and, participants who were randomized to the control group but reported in the physical activity questionnaires to have increased their physical activity level by more than 30 min of extra MVPA per week during the period of interest. The rest of the participants will be analysed as being a “control”. The second analysis of *reported compliance* will include only the participants sufficiently compliant with the protocol that they were allocated to. It will include those randomized into the intervention group who completed at least 2/3 of training volume (e.g. the addition of 100 min per week of vigorous PA) and compare them to those randomized into the control group with no more than 30 min of extra vigorous PA per week than at baseline during the period of interest.

The analysis on the *assumed compliance* will be done according to the analyses of the reported compliance but with participants being defined as compliant if they reach an increase of ≥5% in VO2peak and/or ≥10% in the ventilatory anaerobic threshold from baseline [135].

Model selection Depending on the type of endpoint, mixed linear, logistic, Cox or Poisson regression will be used. All models will include the variables used in the adaptive randomization (age and former cancer diagnosis) and we will test the model assumptions and model fit. The models might be further adjusted for baseline values and important prognostic factors such as sex, socio-economic status, health-behaviours, treatments received, or former treating hospital if we observe an unequal distribution of important confounders between the treatment and control group.

The analysis will be done with Stata Statistical Software version 14 or newer (StataCorp LP, College Station, Texas, USA) and R Statistics (R Core Team, Vienna, Austria, www.R-project.org). A *p*-value <0.05 will be considered as statistically significant. Primary and secondary analyses will be performed when the data collection is finished for all participants.

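### LOCF is made the primary missing-data method because it will be conservative; that is not guaranteed, and where it is conservative the sample size does not allow for the attenuation

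*Protocol article*

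**What the plan says.** The Data analysis section of the protocol article specifies an intention-to-treat primary analysis in which "missing data will be imputed by means of last observation carried forward (LOCF"). The reason given is that "LOCF is an appropriate procedure in this setting because it will lead to more conservative effect estimates (i.e. towards the null"). The premise offered in support of this direction is that "lost to follow-up is more likely to occur in the intervention group", the arm that is expected to improve. The same section promises an attempt to follow up everyone randomised, including those who withdraw from their allocated treatment. It also lists a complete-case analysis among the sensitivity analyses for the primary outcome.

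The Sample size section states that "60 survivors with complete data are required in each study arm", and then: "Assuming that 20% of participants will dropout or have missing data, 75 survivors have to be recruited in each arm". The design values are "For a power of 0.80" and a "two-sided type 1 error probability of 0.05", with a 15% change in the intervention arm and none in controls.

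The model-selection paragraph says: "Depending on the type of endpoint, mixed linear, logistic, Cox or Poisson regression will be used". The Secondary outcomes section analyses the composite score at 6 months as well, so a T6 value exists for anyone who leaves after that visit.

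**The concern.** LOCF moves the estimate towards the null only if the carried value shows less benefit than the missing 12-month value would have shown. Two ordinary situations break that condition. In the first, a benefit at 6 months has faded by month 12, and late leavers carry the better T6 value. In the second, scores worsen over the year in both arms, and more intervention participants are frozen at baseline. In both, LOCF favours the intervention.

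Where the plan's reasoning does hold, there is a second problem. The Data analysis section expects the estimate to be pulled towards the null, but the Sample size section treats dropout only as lost participants and keeps the full 15% effect. The attenuation is accepted in one place and not budgeted for in the other. The primary estimate, its interval and the chance of detecting a real effect depend on this choice.

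**Working it through.** **The plan's own figure.** 60 / (1 − 0.20) = 75 per arm, which reproduces the stated number. No SD or baseline mean is given, so the 60 cannot be derived independently. Inverting the two-means formula at power 0.80 and two-sided alpha 0.05 gives an implied standardised difference d = 0.511 (0.516 with the t distribution).

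**Assumptions, not in the plan.** The dropout split by arm is varied from 20/20 to 40/0 (intervention % / control %), always averaging the planned 20%. The visit carried is either baseline or T6. For the type I error cases, the score SD is 0.6 and the correlation between any two visits is 0.8.

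**1. Power when baseline is carried.** Take the SD of change as 1, let πI and πC be the dropout proportions, and let dropout be unrelated to outcome.

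- LOCF estimate = (1 − πI)d
- SE² = [(1 − πI) + πI(1 − πI)d² + (1 − πC)] / 75
- Example at 30/10: estimate 0.7 × 0.511 = 0.358; SE = √[(0.7 + 0.21 × 0.2616 + 0.9) / 75] = 0.149; ratio 2.41; power Φ(2.41 − 1.96) = 0.67

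| Dropout I/C | Estimate as % of true effect | Power, LOCF | Power, observed data only |
|---|---|---|---|
| 20/20 | 80 | 0.79 | 0.80 |
| 25/15 | 75 | 0.735 | 0.798 |
| 30/10 | 70 | 0.674 | 0.794 |
| 40/0 | 60 | 0.540 | 0.774 |

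With d = 0.516 the LOCF column becomes 0.796, 0.741, 0.681 and 0.547, and the last column 0.806, 0.805, 0.800 and 0.781. By the first formula, 80% power under LOCF would need about 77, 102 and 139 per arm at 20/20, 30/10 and 40/0.

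The loss is smaller if T6 is carried. With half the effect present at T6, simulated power is 0.80, 0.75 and 0.70 at 20/20, 30/10 and 40/0. With the full effect already present at T6 it is 0.88, so nothing is lost.

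**2. Coverage of the 12-month effect.** Suppose that dropouts would have had the same 12-month effect as completers, and baseline is carried. The bias is πI·d. At 30/10 it is 0.3 × 0.511 = 0.153, or 1.03 standard errors, so coverage is Φ(1.96 − 1.03) − Φ(−1.96 − 1.03) = 0.82. At 20/20 it is 0.89 and at 40/0 it is 0.72. With no effect and no drift, coverage is 0.95 at every split.

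**3. Type I error when the true 12-month effect is zero.** The variance of change is V = 2 × 0.6² × (1 − 0.8) = 0.144.

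*Fading benefit, T6 carried, T6 effect −e.* The estimate is −πI·e and SE² = [2V + πI(1 − πI)e²] / 75.
- e = 0.2 at 30/10: estimate −0.06, SE 0.063, ratio 0.95, type I error about 16%. At 20/20 it is about 10%.
- e = 0.1 at 30/10: estimate −0.03, SE 0.062, about 7 to 8%.

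*Both arms worsen by w, baseline carried.* The estimate is −w(πI − πC), and each arm's variance is (1 − π)V + π(1 − π)w².
- w = 0.2 at 30/10: estimate −0.04, SE 0.057, ratio 0.70, about 11%.
- w = 0.1 at 30/10: estimate −0.02, SE 0.056, about 6 to 7%.
- With equal dropout, uniform drift creates no false effect.

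With no drift and no fading, type I error is 5% at every split.

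**The case against.** The strongest reply is that the plan's own premises largely protect it. The Sample size section assumes no change in controls, and the Primary outcome section uses age- and gender-referenced z-scores, which absorb part of any ageing trend. Under those premises and a true null, type I error is 5%. The larger figures need a 6-month effect as big as the design effect (0.516 × √0.144 ≈ 0.196) to vanish, or a drift of that size in one year. This stands: the false effect is a conditional risk.

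A second reply is that participants who stop exercising may return to baseline. Carrying baseline would then match the effect in everyone as randomised, and the coverage shortfall would not arise. This also stands as a possibility, but the plan does not argue it. It argues from conservatism.

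Three stronger readings are tempting, and the documents do not support them:

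- A reader might infer that LOCF understates the standard error. For the change-score comparison examined here it does not. At SD 0.6, correlation 0.8 and 30/10 dropout, the empirical and the reported standard errors are both 0.056. The under-coverage comes from bias.
- A reader might infer that the stated power is lost on the plan's own figures. The plan gives only the direction of unequal loss. At an even 20/20 split the loss is immaterial.
- A reader might infer that LOCF is the only provision for missing primary data. The complete-case sensitivity analysis and the attempted follow-up after withdrawal both lessen the problem, although neither changes the primary analysis.

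**Conclusion.** The concern holds in a conditional form. The plan rests its primary missing-data method on a guarantee that LOCF does not give. The estimate can move in favour of the intervention under fading, or under a common worsening with unequal dropout. At 30/10 the type I error is about 6 to 8% for shifts of 0.1 and 11 to 16% for shifts of 0.2.

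Where the guarantee does hold, its price is missing from the sample size. With baseline carried, power is about 0.73 to 0.74 at 25/15, 0.67 to 0.68 at 30/10 and 0.54 to 0.55 at 40/0, against about 0.77 to 0.81 for an analysis of observed data. Intervals under-cover only where LOCF is biased for the 12-month effect.

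All these sizes rest on the assumed split, the visit carried, the SD and the correlation. Because invalidity is conditional and a complete-case check is already planned, this should be fixed but is not fatal to the design.

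**What to change.** Make the primary analysis a likelihood-based linear mixed model for repeated measures of the composite score at T6 and T12. Include all randomised participants and all observed data, with baseline score, minimisation factors, visit and arm-by-visit interaction as terms, and name the T12 contrast as primary. Keep LOCF only as a sensitivity analysis, and delete the statement that it will be conservative.

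Reference-based multiple imputation may be added as a sensitivity analysis for departures from missing at random. With no change expected in controls, it would attenuate the effect in much the same way as LOCF, so it does not restore power.

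The cost is a change of wording before analysis and slightly more analysis work. No new data are needed: the plan already names mixed linear models and already collects the T6 scores. The downside is reliance on a missing-at-random assumption. If dropouts really do return to baseline for reasons that the observed data do not capture, the mixed model would overstate the effect in everyone randomised, which is why the sensitivity analyses should stay.
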